
### Proposed tools for measuring implementation outcomes

There are various tools that have been utilized to assess various implementation outcomes across the literature. We will be using different adapted tools including the Acceptability of Intervention Measure (AIM), Intervention Appropriateness Measure (IAM), and Feasibility of Intervention Measure (FIM), psychometrically validated tools developed to assess key early-stage implementation outcomes. Each of these instruments consist of four items, rated on a five-point Likert scale from “completely disagree” to “completely agree.” The AIM captures the degree to which stakeholders find an intervention agreeable or satisfactory, making it a useful measure of perceived acceptability. The IAM evaluates whether an intervention is perceived as a good fit or relevant for a given context or problem, thereby assessing its appropriateness. The FIM measures the perceived practicality and ease with which an intervention can be successfully implemented in a specific setting. These tools are designed for ease of use, brevity, and reliability, making them highly suitable for integration into implementation research and practice across diverse settings [37]. In addition, other tools will be utilized depending on the expected outcome measures including the Clinical Sustainability Assessment Tool (CSAT), Short Form, and the Program Sustainability Assessment Tool (PSAT), Short Form, for model implementation sustainability assessment (Table 2).

**Table 2 Tab2:** Implementation outcomes and proposed assessment tools for the model of care

	Constructs	Assessment tools/Measures	Source of data	Method
RE‑AIM Implementation Evaluation Framework with Proctor et al. style implementation outcomes	Reach	Participation rate: % of individuals invited who actually undergo screening for the target NCDs.	Registry lists and clinical records	-
	Effectiveness	Follow-up rate: % of screen-positive individuals who receive timely confirmatory diagnosis and/or treatment.	Clinical records	-
		Proportion of people with controlled hypertension and diabetes among those diagnosed.	Clinical records	-
				-
	Adoption	Proportion of implementing agents/staffs that deliver model of care components.	Clinical records	-
	Implementation			
	✓ Acceptability	Acceptability of Intervention Measure (AIM) 4-items [37].	Implementing site staff members	Survey
	✓ Appropriateness	Intervention Appropriateness Measure (IAM) 4-items [37].	Implementing site staff members	Survey
	✓ Feasibility	Feasibility of Intervention Measure (FIM) 4-items [37].	Implementing site staff members	Survey
	✓ Cost	Cost capture survey [38], and time-driven activity-based costing methods [39].	Research team and implementing site staff members	Survey
	✓ Fidelity	A checklist developed based on the interventions of the developed model of care package.	Implementing site staff members/leaders	Survey
EPIS and RE-AIM Framework	Sustainment	Clinical Sustainability Assessment Tool (CSAT) Short Form: 7 domains, 21 items total [40].	Implementing sites	Survey
		Program Sustainability Assessment Tool (PSAT) Short Form: 8 domains, 40 items total [40].	Implementing sites	Survey
		And/or other program-based tools.	Implementing sites	Survey

### Cluster size and number of expected participants

We are proposing to include six faith-based organisations having large CALD community followers as intervention sites, as these settings provide trusted community environments that are well suited for delivering an outreach model of care. A matched set of six comparable faith-based organisations will be selected as control sites to allow for meaningful comparison. Faith-based organisations are institutions that are guided by religious principles and provide prayer and other religious activities, as well as services such as social support, education, and healthcare. However, while some of such organizations might focus on specific CALD communities, many may offer services to the wider population regardless of cultural or religious background. Therefore, we are aiming to consider such faith-based settings, and the final selection of which specific organisations to include and not to include will be decided during the later stages of model co-development process, based on relevance and feasibility. All selected organisations will be invited to participate and collaborate throughout the implementation research process, including planning and co-developing the intervention components. Comparability between intervention and control sites will be ensured by selecting organisations with similar CALD population size, demographic characteristics, and levels of community engagement, thereby supporting baseline equivalence across clusters and the assumptions required for a robust Difference-in-Differences approach-based data analysis. The details of the implementation process, including the selection of intervention and control sites, will be determined once the components of the multi-packaged model of care are identified and the model of care is co-developed in consultation with relevant stakeholders.

With regards to the sample size for this quasi-experimental study using the Difference-in-Differences approach, we have considered a hypertension prevalence of 34%, and an assumed baseline screening rate of 50% based on previous literature which shows that only one in two people detected to have hypertension are aware of their condition among the Australian population [4, 5]. Our target is to increase hypertension screening rates among CALD communities from 50% at baseline to at least 70% post-intervention, representing a 20% increase. To detect this difference with 80% power and a 5% significance level, we first calculated the sample size for comparing two independent proportions, assuming individual randomization. This yielded an unadjusted sample size of approximately 182 participants (91 per group).

Nevertheless, given the study’s clustered design involving 12 sites (six intervention and six control clusters), it is necessary to adjust for the expected intra-cluster correlation (ICC), which accounts for the similarity of responses within clusters. This adjustment is done by applying a design effect, calculated as: Design Effect (DE) = 1 + (m − 1) × ICC, where “m” is the average number of participants per cluster. In this study, we expect to recruit 100 participants per cluster and assume an ICC of 0.02 [41]. Applying these values, the design effect becomes: DE = 1 + (100 − 1) × 0.02 = 1 + 99 × 0.02 = 2.98. Applying this yielded an adjusted total sample size of approximately 543 participants, or about 272 per arm. Therefore, with the 100 expected participants from each cluster, the final planned sample size of 1,200 exceeds the minimum requirement and ensures sufficient power to detect the expected effect while remaining practical. Furthermore, the qualitative component will also include in-depth interviews, and stakeholder workshops with CALD communities, healthcare providers, and policymakers to explore perceptions, implementation processes, barriers, and enablers.

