## Methods

### Study design and process

This project will employ a four-phased strategy which has been utilized by other implementation research scholars with each phase focussing on distinct research objectives [22]. A two‑period, before‑and‑after Difference‑in‑Differences design with repeated cross‑sectional sampling at baseline and follow‑up will be utilized to evaluate the impact of the implemented model of care on access to and utilization of hypertension and diabetes screening among CALD communities in Brisbane city. Australia. The Difference-in-Differences approach is a quasi-experimental method that can be utilized to estimate causal effects using observational data when randomization is not feasible. It helps compare the changes in outcomes over time between a treatment group (affected by the intervention) and a control group (not affected) [23–25]. This design is appropriate for our study as it enables comparison of group‑level changes without requiring follow‑up of the same individuals over time. The Exploration, Preparation, Implementation, Sustainment (EPIS) framework will be utilized to guide the phase-wise execution of the overall implementation process of the project work. This framework provides a structured approach to understanding and navigating the complexities of implementing evidence based practices by considering multiple contextual factors [26]. Additional complementary frameworks will also be utilized in different phases depending on the objectives of each phase and other contextual requirements.

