##### Capacity building for project implementers

The project steering committee (comprising of a multidisciplinary team of project implementers from different implementing sites) will provide a comprehensive training to the relevant stakeholders including the health workers who are directly involved in providing health care services for the selected NCDs. If this is not possible, the training will be provided by the project advisory members using online training platforms. The training will be provided with a combination of four to five interactive sessions, and didactic lectures to enhance the adoption of the multi-packaged interventions. The healthcare professionals and other stakeholders undergoing training will be assessed for knowledge and practice change using a pre-developed assessment module. A score of > 80% in the training assessment will be considered adequate and, if the score is < 80%, a re-training session will be provided [22].

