##### Implementation of the multi-packaged model of care

Baseline data will be collected, and the model of care will be implemented in those settings in collaboration with different stakeholders, after completion of the trainings. The process of model implementation to enhance access to and utilization of health care services for hypertension and diabetes mellitus screening, and initiation of treatment for those diagnosed among CALD communities and other secondary objectives will be recorded. In addition, any challenges experienced in the adoption of the interventions will be documented and communicated for concerned bodies including the project implementing agencies.

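### Control organisations are not kept out of co-developing the package, and baseline is placed after staff training, so the difference-in-differences contrast may be contaminated, probably but not certainly towards no effect

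*Protocol article*

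**What the plan says.** **Who co-develops.** Cluster size and number of expected participants proposes six intervention organisations and then six controls: "A matched set of six comparable faith-based organisations will be selected as control sites to allow for meaningful comparison". A few sentences later it says: "All selected organisations will be invited to participate and collaborate throughout the implementation research process, including planning and co-developing the intervention components". The controls are themselves selected organisations, and no exception is made for them. The section closes by saying that details of the process, "including the selection of intervention and control sites, will be determined once the components of the multi-packaged model of care are identified", which puts site selection after co-development.

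**What a control is.** Study design and process describes the method as comparing changes over time "between a treatment group (affected by the intervention) and a control group (not affected".

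**When baseline is taken.** Three places bear on this:
- Implementation of the multi-packaged model of care: "data will be collected, and the model of care will be implemented in those settings in collaboration with different stakeholders, after completion of the trainings".
- In the Phase III introduction, baseline is put in the preparation step, which also contains staff training.
- Outcomes of model implementation says only that baseline precedes implementation.

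**What training is for.** Capacity building for project implementers directs it to relevant stakeholders, including health workers who deliver the care, "to enhance the adoption of the multi-packaged interventions". Training of control sites is not mentioned.

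**How the assumption is checked.** The data analysis plan acknowledges that there is a single pre-intervention time point and assesses parallel trends indirectly, through baseline comparisons and sensitivity analyses.

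**The concern.** A difference-in-differences estimate relies on a control arm whose change over time shows what would have happened without the intervention, and on a baseline that predates any effect of it. The text weakens both.

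The example components under Expected outcomes of Phase II include services around faith-based settings and promotion through community leaders. Leaders of a control organisation who helped design these could start parts of them. Health workers trained to adopt the package could prompt screening before baseline is recorded, and that screening would count as part of the 'before' level.

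The planned analyses cannot help. The GEE model, the mixed model, covariate adjustment, standardised mean differences, imputation and weights do not measure exposure. With one pre-period, an early training effect in the intervention arm looks the same as a pre-existing site difference.

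**Working it through.** **1. The plan's own figure.** Inputs from Cluster size and number of expected participants: 50% versus 70%, 5% significance (taken as two-sided), 80% power, 100 per cluster, ICC 0.02.
- Per group: (0.25 + 0.21) × (1.96 + 0.8416)² / 0.20² = 90.26, rounded up to 91, so 182 in total.
- Design effect: 1 + 99 × 0.02 = 2.98.
- 182 × 2.98 = 542.4 (543), and 91 × 2.98 = 271.2 (272 per arm).

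The stated figures reproduce. This point does not dispute them.

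**2. Where exposure enters the estimate.** Let E be the true effect (20 points), t0 the training effect already present in the intervention baseline, and c0 and c1 the exposure effects in controls at baseline and follow-up. Then

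expected DiD = E − t0 − (c1 − c0).

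The documents give no sizes for t0, c0 or c1; the values below are assumptions.

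| t0 | c0 | c1 | Expected DiD (points) |
|---|---|---|---|
| 0 | 0 | 0 | 20 |
| 5 | 0 | 0 | 15 |
| 0 | 0 | 5 | 15 |
| 5 | 5 | 10 | 10 |
| 0 | 5 | 5 | 20 (cancels) |
| 5 | 5 | 0 | 20 (cancels) |
| 0 | 5 | 0 | 25 (away from zero) |

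If training raises screening before baseline, that route can only attenuate. The control route depends on whether exposure grows, stays level or fades.

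**3. What a net leak of 5 points costs.** Let m be the number per site per round and r the correlation between a site's two rounds. The variance of the DiD is

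[Σ p(1 − p) / (6m)] × [1 + (m − 1) × 0.02 − m × 0.02 × r],

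summed over the four arm-by-round cells. Power uses a non-central t with 10 df (12 sites less 2 arms; critical value 2.228). The value of r is not in the documents, so the range 0 to 1 is shown. The article does not say whether 1,200 is per round or over both rounds, so m = 100 and m = 50 are both shown.
- No leak (50/70/50/50%): Σ p(1 − p) = 0.96.
- 5-point leak (50/70/50/55%): Σ p(1 − p) = 0.9575.
- Multiplier: 2.98 (r = 0) to 0.98 (r = 1) for m = 100; 1.98 to 0.98 for m = 50.
- Standard error without leak: √(0.96/600 × 2.98) = 0.0690 to √(0.96/600 × 0.98) = 0.0396 for m = 100; 0.0796 to 0.0560 for m = 50. With the leak it is almost unchanged.

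| m | Power at 20 points, r = 0 to 1 | Power at 15 points, r = 0 to 1 |
|---|---|---|
| 100 | 74.2% to 99.5% | 50.2% to 92.6% |
| 50 | 62.1% to 89.5% | 40.0% to 67.7% |

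**The case against.** A reader might infer that neither arm's 'before' period is unexposed and that the estimate must therefore be pulled towards zero. The documents do not support this, for four reasons.
- Organisations are only invited, and knowing a package is not delivering it. Delivery needs partner health facilities, registration and invitation of eligible adults, trained staff and site facilitators. Nothing gives these to controls.
- The sentence that fixes sites after co-development can mean that no organisation is yet a control while the package is being built.
- Baseline is said to precede implementation, so it precedes service delivery; only its order relative to training is in doubt. Reach is screened over invited, and invitation is described in the implementation phase, so early uptake is a possibility and not a stated fact. Operational timing is referred to Supplementary File 1, which is not shown.
- By the algebra above, control exposure in the 'before' period alone cancels or biases away from zero.

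The size of any leak is also unknown. At 2 points, with m = 100 and r = 0.5, power is still 82%.

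All of this limits the claim without removing it. Fixing the arms late does not protect the controls, because nothing requires them to come from organisations that stayed out of co-development. The invitation also covers the whole research process, which makes exposure that grows up to follow-up plausible. And none of the three baseline statements puts baseline before training.

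**Conclusion.** The point holds as a weakness in stated rules. As written, the plan admits control organisations to co-development, contrary to its own definition of a control, and is inconsistent about whether sites are chosen before or after that work. It also puts baseline after training in one section and leaves the order open in two others. Either route can bias a contrast that has a single pre-period and no planned analysis able to reveal the bias.

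Attenuation is the likely direction, but the text does not determine it. Under an assumed 5-point net leak, the expected effect falls from 20 to 15 points. Power is then below the 80% target over the whole range of r with 50 per site per round, and over part of it with 100. These figures illustrate the stake; they rest on the assumed leak, the protocol's ICC of 0.02, the t reference with 10 df and an unknown between-period correlation. The published sample size calculation is not itself wrong on this account.

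**What to change.** (a) In Cluster size and number of expected participants, restrict co-development and site-facing materials to intervention organisations and stakeholders outside the control sites. Draw controls from organisations that did not co-develop the package. State that controls contribute to data collection only, with the package offered to them after follow-up.

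(b) In Implementation of the multi-packaged model of care, place baseline at all 12 sites over the same calendar period, after site selection and consent but before any staff training. Bring the Phase III introduction, Outcomes of model implementation and the site-selection sentence into line with this.

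Requiring baseline before any contact with community leaders would go too far: leaders take part in Phase II, sites are chosen after it, and the organisations' consent is sought before people are registered.

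The cost is mainly wording and re-ordering, since sites are not yet chosen. The downside is less input from control organisations and a narrower pool from which to find matched controls.

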### Data analysis plan for the main model

The Difference in Differences approach will be used to compare changes in hypertension and diabetes screening uptake between intervention and control sites over time with a repeated cross-sectional design. A Generalized Estimating Equations model will be utilized as the primary analysis method with site clustered robust standard errors and an appropriate small sample correction to account for the limited number of clusters. In addition, a generalized linear mixed model with a site level random intercept will be used as a sensitivity analysis. Key participant characteristics including age, sex, region of birth, education, primary language, and baseline comorbidities will be included as covariates. Results will be presented as adjusted marginal effects with 95% confidence intervals. Baseline equivalence between intervention and control sites will be examined using standardized mean differences, and any identified imbalances will be controlled for in the modelling. The parallel trends assumption will be assessed indirectly through these baseline comparisons and sensitivity analyses as only one pre intervention time point is available. For secondary outcomes, follow up completion, treatment initiation, and clinical control will be derived from the nested cohort of screen positive individuals and will be summarised and analysed as site period proportions. Missing data will be handled using multiple imputation with additional sensitivity analyses to evaluate the robustness of findings. If individual level data are pooled across sites with fixed per site samples, design weights proportional to the site population of eligible invitees will be used to account for unequal selection probabilities (See Supplementary File 1).

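### The sample size is worked out for two independent proportions rather than the planned Difference-in-Differences contrast, so 543 is not its minimum and the power claimed for 1,200 is unsupported

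*Protocol article*

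**What the plan says.** The section on study design and process of the protocol article fixes the evaluation: a "Difference‑in‑Differences design with repeated cross‑sectional sampling at baseline and follow‑up will be utilized". The data analysis plan repeats the contrast. The model will "compare changes in hypertension and diabetes screening uptake between intervention and control sites over time with a repeated cross-sectional design", fitted by generalized estimating equations with "site clustered robust standard errors and an appropriate small sample correction to account for the limited number of clusters".

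The section on cluster size and expected participants presents its calculation as the one for this DiD study. The target is a rise "from 50% at baseline to at least 70% post-intervention, representing a 20% increase". Power is set at 80% and the significance level at 5%, and the sizing step reads: "we first calculated the sample size for comparing two independent proportions, assuming individual randomization". This gives 91 per group, 182 in all. With 100 participants per cluster and an ICC of 0.02 the design effect is 2.98, and "Applying this yielded an adjusted total sample size of approximately 543 participants, or about 272 per arm". The section concludes that "the final planned sample size of 1,200 exceeds the minimum requirement and ensures sufficient power to detect the expected effect".

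It gives no expected change in the control sites and no correlation between rounds within a site. It does not say whether the 100 per cluster is recruited in each round or over both.

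**The concern.** A comparison of two independent proportions has two sources of sampling error. A DiD on repeated cross-sections has four, because each arm contributes a baseline and a follow-up sample. It also depends on how far a site's own level persists from one round to the next, and on the reference distribution used with 12 sites. None of this enters the calculation.

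The 20-point figure is described as a change over time but used as a difference between two groups. The two agree with the DiD effect only if uptake in the control sites does not move, which the article never states.

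At stake is the only power justification given for the DiD comparison of screening uptake. If 543 is taken as the floor, a shortfall in recruitment from 1,200 towards 543 would look harmless when it is not.

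**Working it through.** **Inputs from the article:** 50% and 70%; power 80%; significance level 5% (two-sided reproduces the figure); 6 + 6 sites; 100 per cluster; ICC 0.02.

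**Assumptions made here, because the article gives no value:** control sites stay at 50%; CAC (the correlation between a site's effects in the two rounds) from 0 to 1; t with 10 degrees of freedom (12 sites less 2 arms) as one form of small-sample correction.

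**1. The plan's own figure.** (1.960 + 0.842)² = 7.849.
- Per group: 7.849 × (0.25 + 0.21) / 0.20² = 90.3, so 91 per group and 182 in all.
- Design effect: 1 + 99 × 0.02 = 2.98.
- 182 × 2.98 = 542.4, so 543. The article's arithmetic reproduces.

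**2. The DiD before clustering.** The cells are 50%, 50% (control) and 50%, 70% (intervention). The summed variance is 3 × 0.25 + 0.21 = 0.96, against 0.46 above.
- Per cell: 7.849 × 0.96 / 0.04 = 188.4, so 189.
- Four cells: 756, against 182.
- With the article's own design effect, which amounts to CAC 0 at 100 per site per round: 756 × 2.98 = 2,253 over both rounds, or about 1,127 per round.

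**3. The DiD with clustering.** Let m be the number per site per round, and v₁, v₂ an arm's two values of p(1 − p). Each arm contributes

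{ (v₁ + v₂)/m × [1 + (m − 1) × ICC] − 2 × ICC × CAC × √(v₁v₂) } / 6

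to the variance, and the two arms are added.

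Example with m = 50 and CAC 0.5:
- Control: (0.01 × 1.98 − 0.005)/6 = 0.002467.
- Intervention: (0.0092 × 1.98 − 0.00458)/6 = 0.002272.
- SE = √0.004739 = 0.0688.
- Normal power: Φ(0.20/0.0688 − 1.96) = 83%.

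**4. Total over both rounds (24 × m) for 80% power:**

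| CAC | Normal | t, 10 df |
|---|---|---|
| 0 | 1,992 | 4,032 |
| 0.5 | 1,080 | 1,488 |
| 0.8 | 864 | 1,080 |
| 1 | 744 | 912 |

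**5. Power for a 20-point DiD, normal (t on 10 df):**

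| Size | m | CAC 0 | CAC 0.5 | CAC 0.8 | CAC 1 |
|---|---|---|---|---|---|
| 543 in total | 22.6 | 51% (44%) | 58% (50%) | 63% (55%) | 67% (58%) |
| 543 per round | 45.2 | 69% (60%) | 80% (72%) | 88% (80%) | 92% (86%) |
| 1,200 in total | 50 | 71% (62%) | 83% (75%) | 90% (83%) | 95% (89%) |
| 1,200 per round | 100 | 83% (74%) | 94% (89%) | 99% (97%) | >99% (>99%) |

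**6. Dependence on flat controls.** If control uptake rose by 5 points (a scenario, not a figure from the article), the DiD would be 15 points. At CAC 0.5, power would be 59% (t: 50%) for 1,200 in total and 76% (t: 67%) for 1,200 per round.

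**The case against.** A reader might infer that the study is underpowered, or that the claim for 1,200 is false. The article does not support either. If 100 per cluster means per site per round, the article's own design effect gives a DiD need of about 1,127 per round, which 1,200 exceeds. Normal-approximation power is then 83% even at CAC 0. The same sites are measured twice, so some persistence is plausible and would raise power. This part of the objection stands.

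It is also fair to say that 543 is not explicitly labelled as covering both rounds. Read as 543 per round, it reaches 80% at CAC of about 0.5 or more (about 0.8 with t on 10 df). But the article calls it a total, states no CAC, and does not derive it from the DiD contrast, so this reading does not rescue it as a stated minimum.

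CAC, 10 degrees of freedom and the control-arm scenarios are assumptions made in this check, because the article says only that a suitable correction will be used. The split between rounds may be given in Supplementary File 1, which is not shown, so its absence here carries little weight alone. Finally, it is an inference that the calculation describes a follow-up-only comparison between arms; the text says only that two independent proportions are compared. None of this removes the mismatch, because the article prints a complete calculation for one contrast and draws its power conclusion for another.

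**Conclusion.** The point holds as a mismatch between design and sample size, not as an arithmetic slip: 91, 182, 2.98 and 543 are all computed correctly, but for a different contrast. As a total over both rounds, 543 falls below the DiD requirement at every CAC from 0 to 1.

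For 1,200, the assurance of sufficient power is unsupported but not shown false. Whether it reaches 80% depends on the number per round, the between-round correlation and the small-sample method. Under the t reference it falls short at CAC 0 and 0.5 if 1,200 covers both rounds, and only at CAC 0 among the values tabulated if it is per round. All these results rest on ICC 0.02 and flat control sites.

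**What to change.** Replace the two-proportion calculation with one for the four-cell repeated cross-sectional DiD. Delete 543 and the statement that the planned size exceeds it. State:
- the number of participants per site per round, and so whether 1,200 is per round or over both;
- the assumed change in the control sites;
- the effect as a DiD of 20 percentage points, not a 20% increase;
- a CAC range with its justification;
- the small-sample method and its degrees of freedom.

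Then restate the power that 1,200 delivers over that range. For example, if 1,200 covers both rounds, CAC is taken as 0.5 to 0.8 and t on 10 df is used, the figure is 75% to 83%.

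The change is to text only, but the stated power may become less favourable. It is best made before baseline data collection, while the number of sites or the sample per round can still be changed.
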